## 11.6 Imaging Plan

Patients will undergo diagnostic CECT neck and thorax prior to inclusion in the study to rule out distant metastases. Use of other imaging modalities including bone scan / PET CT for detection of metastases is left to the discretion of the treating physician based on the clinical findings for a given patient. At 2 monthly intervals the patient would undergo radiological response assessment imaging if the patient has not grossly clinically progressed.

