| Study procedure          | 
Intervention : Patients would receive the intended oral therapy
These patients would be monitored for response and toxicity (CTCAE version 4.02) at D8 and D30. Following which they would be assessed every month.
 
Biomarker : All patients would undergo serum biomarker investigations at least 1 day before administration of oral therapy, then at at D8, D30 and for next 3 months
 
Biopsy : Done at baseline, then at at D8 and at progression.
 
Response (Radiology) : Done at baseline and then at 1 monthly intervals
                                                              |
| Sample Size              | Around 20-30 patients would be required for stage 1. In the second stage the combination of MCT-E would be administered in 76 patients.                                                                                                                                                                                                                                                                                                                                                                                                                                                                                                                |
| Date of first enrollment | Post IRB/IEC and grants approval.                                                                                                                                                                                                                                                                                                                                                                                                                                                                                                                                                                                                                      |

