### Pretreatment Criteria

All patients will have to fulfil the following criteria prior to starting MCT. Each 4 weeks of treatment would be considered as one cycle.

Prior to first cycle:

1. Hemoglobin: > 10 g/dL
2. Total Leucocyte Count : > 3000 / cumm
3. Platelet Count : > 1,00,000 / cumm
4. AST / ALT : < 2.5 times upper normal limit of institutional value
5. Bilirubin: Total < 1.5 times upper normal limit of institutional value
6. Calculated serum creatinine clearance above 30 ml/min

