## 12 Study procedure

### 12.1 Clinical Intervention

Patients on MCT would be monitored for response ( RECIST version 1.1) and toxicity (CTCAE version 4.03) at C1D8, D30 and subsequently monthly till progression.

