| Serum markers ( ELISA +                                   | ✓         | -    | ✓    | ✓                    | -                       | ✓           |

|                  |   |   |   |   |   |   |
|------------------|---|---|---|---|---|---|
| Flow)            |   |   |   |   |   |   |
| MRI/CT Head Neck | ✓ | - | - | ✓ | ✓ | ✓ |
| MCT Chemotherapy | - | ✓ | ✓ | ✓ | ✓ | - |

Table 7 : Study calendar

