## 15 Sample size calculation

**Total sample size** : Stage 1 ( 20-30 patients) + Stage 2 ( 76 patients). In stage the continuous reassessment model will be used hence the sample size would be maximum of 30 and minimum around 20. The exact calculations done in both stages are described below in details.

Stage 1 : Flexible-finite sample based approach will be adopted to select the circulating endothelial cells (CEC) interval boundaries and further to use optimum interval design. During the trial, we will continuously update the posterior estimates of decline in CEC and clinical benefit rate and assign patients to the most appropriate dose combination (Figure 1). The Bayesian adaptive screening design will be used to simultaneously select among possible treatment dose combinations. The design is based on formulating the selection procedure as a Bayesian hypothesis testing problem in which the superiority of each treatment combination is equated to a single hypothesis. During the trial conduct, we intend to use the current values of the posterior probabilities of all hypotheses to adaptively allocate patients to treatment combinations. The dose-finding decision will be decided on the twin endpoints the clinical benefit rate at 2 months and proportional decline in CEC at D8 of first cycle. Figure 2 will be used for decision making.

Stage 2: It was assumed that the 3-month progression-free survival (PFS) rate of a standard cancer therapy is 0.50 (H0). An improvement to 0.60 would be considered clinically significant (H1). Assume both the null and alternative PFS distributions follow an exponential distribution. The 1-sided type I error rate of 0.05 and type II error rate of 0.1. Prior assumption includes a fixed enrollment rate of 3 patients per month. We require a stop of 3 months at the end of Stage 1. The library("OptInterim") has been used to calculate the sample size. A 20%extra patient would be taken to account for lost to follow up data. Hence **a total of 76 ( 63 patients +13 patient) sample size is found suitable to carry out the study for stage II with single arm drug therapy.**

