## 16 Outcome measures

### 16.1 Primary outcome :

In stage I the OBD of methotrexate would be identified using response assessment criteria RECIST version 1.1 and flow cytometry measurement of CEC. So a twin primary endpoints of clinical benefit rate at 2 months ( CR or PR or SD persisting till 2 months) and proportional decline in CEC will be used for determination of OBD.

In stage 2 the PFS would be measured in days from date of recruitment in the study till the date of progression (clinical or radiological or both). Median PFS would be estimated by Kaplan Meier survival method.

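### Response imaging is 2-monthly in Section 11.6 but monthly in the concept sheet and every cycle in Table 7; the 2-monthly version biases 3-month PFS upward by up to 0.13

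*Protocol*

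**What the plan says.** The protocol gives two imaging frequencies.

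- Section 11.6 (Imaging Plan): "At 2 monthly intervals the patient would undergo radiological response assessment imaging if the patient has not grossly clinically progressed".
- Section 3 (Concept sheet, study procedure row), on radiological response: "Done at baseline and then at 1 monthly intervals".
- Section 13, Table 7: the row "MRI/CT Head Neck" is ticked pre-study, at day 1 of the first 3 cycles, at day 1 of subsequent cycles, and at progression. The Pretreatment Criteria fix the cycle length: "Each 4 weeks of treatment would be considered as one cycle".

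Sections 11.1 and 12.1 also require RECIST 1.1 response monitoring "at C1D8, D30 and subsequently monthly till progression", without saying whether each monthly check includes a scan.

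The Stage 2 endpoint depends on these dates. Section 16.1 counts PFS from recruitment "till the date of progression (clinical or radiological or both"), and adds "Median PFS would be estimated by Kaplan Meier survival method". Section 15 sizes the stage on a landmark: "It was assumed that the 3-month progression-free survival (PFS) rate of a standard cancer therapy is 0.50 (H0"), against 0.60 under H1, both exponential, with one-sided alpha 0.05 and type II error 0.1. Section 6 and the concept sheet state the question as whether median PFS exceeds 3 months.

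**The concern.** All these passages are current text, and none says which prevails. An investigator who follows Section 11.6 and one who follows Table 7 would date the same radiological progression differently.

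The two versions do not serve the endpoint equally well. Under Section 11.6 scans fall at months 2, 4, 6 and so on, and month 3 sits in the middle of a gap. A patient whose tumour progresses at, say, 2.5 months, with nothing evident on examination, still counts as progression-free at month 3 and receives an event date at month 4. The error can only delay event dates. It therefore raises 3-month PFS, and it pushes the Kaplan-Meier median past 3 months, which is the direction the trial would read as success. In a single-arm trial no concurrent arm carries the same bias to cancel it.

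**Working it through.** **Inputs from the protocol.** H0: S(3) = 0.50; H1: S(3) = 0.60; exponential PFS; one-sided alpha 0.05; n = 63, or 76 with the added 20% (Section 15). Scans at months 2 and 4 (Section 11.6) or every 4 weeks (Table 7).

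**Input not in the protocol.** f is the share of progressions dated clinically, and on time, without waiting for a scan. It is assumed not to depend on when the patient progresses, and is varied over its full range of 0 to 1.

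**The plan's own figures.** Under H0, S(t) = 0.5^(t/3), so S(3) = 0.50 and the median is 3 months. This agrees with the question in Section 6. The inflation also reproduces: 63 × 1.2 = 75.6, rounded to 76. How the 63 was derived is a separate matter, and nothing here depends on it.

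**Recorded 3-month PFS on the 2-monthly schedule.** Progressions found only by scan are recorded by month 3 only if they occurred by month 2, so for them the recorded value is S(2) = 0.5^(2/3) = 0.630. Clinically dated progressions give S(3) = 0.500. Together:

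recorded S(3) = f × 0.500 + (1 − f) × 0.630

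This equals 0.60 when f = (0.630 − 0.600)/(0.630 − 0.500) ≈ 0.23.

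**What this could do to a test.** The protocol does not name a binomial test. As an illustration only, take the exact binomial rule with one-sided size at most 0.05: reject at 39 or more of 63, or at 46 or more of 76.

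| f | Recorded S(3) under H0 | Rejects, n = 63 | Rejects, n = 76 |
|---|---|---|---|
| 1.00 | 0.500 | 3.8% | 4.2% |
| 0.75 | 0.532 | 10.5% | 12% |
| 0.50 | 0.565 | 23% | 28% |
| 0.25 | 0.597 | 42% | 49% |
| 0 | 0.630 | 63% | 72% |

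**The median criterion.** For any f below 1 the expected recorded 3-month PFS of a null regimen is above 0.50, so its Kaplan-Meier median tends to read later than 3 months.

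**Under H1.** The same shift applies: with f = 0, recorded S(3) = 0.6^(2/3) = 0.711.

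**The 4-weekly schedule.** The last scan before month 3 (taken as 91.3 days) falls near day 84. With scan-only detection the recorded value is 0.5^(84/91.3) = 0.528. A scan at month 3 itself gives 0.500.

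**The case against.** The strongest reply is that clinical progression counts. Section 16.1 says so, Section 11.6 exempts patients who have obviously progressed on examination, response is checked monthly, physical examination is ticked at every cycle, and Section 10.1 allows lesions to be measured by calipers. Oral cavity tumours recorded that way may well be caught between scans. This stands. A reader might infer from the schedule that an ineffective regimen would show a 3-month PFS of 0.63, above the H1 target. The documents do not support that, because 0.63 is the ceiling reached only if no progression is dated clinically.

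Three further objections also stand.

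- The rejection rates come from a stand-in test. Section 15 names the OptInterim library with exponential distributions, and Section 16.1 names a Kaplan-Meier median. The binomial rule has only 43% power at 0.60 with n = 63 and 51% with n = 76, so it is plainly not the planned test. The rates show direction and scale; they are not this trial's type I error.
- The protocol does not say how often patients behind the 0.50 were assessed. If that was also about every 2 months, part or all of the shift is already in H0.
- Table 7's schedule is not free of bias either (0.528 if scan-only).

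Some other tempting readings fail. The median need not fall on a scan date, since clinically dated events can fall on any day. The inconsistency is not between sites, because Section 9 names one centre; it would arise between clinicians or patients. Nor does Table 7 show narrower follow-up than baseline imaging, because the same head-and-neck row also covers the pre-study scan.

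None of this removes the contradiction or changes the direction of the bias.

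**Conclusion.** The concern holds in bounded form. That the imaging frequencies contradict each other is certain from the text. If the 2-monthly version is followed, 3-month PFS is biased upward by between 0 and 0.13 under the protocol's exponential H0. The size depends on the share of progressions dated clinically, which is not stated: 0.03 if three quarters are, 0.065 if half are. Only below about 23% does a null regimen's expected value pass 0.60. In the illustrative test at n = 63, false positives are about 10% at a 75% share, 23% at 50% and 63% at zero, against a nominal 5%.

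These sizes rest on exponential PFS, a clinical share that does not vary with time, clinical dating without delay, and a 0.50 reference that does not already carry the same delay. Confidence is high for the contradiction and the direction, and lower for the size.

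This should be settled in the protocol. Assessment timing is a trial procedure, and a scan not taken around month 3 cannot be recovered in the analysis.

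**What to change.** State one imaging schedule, in the same words, in Section 3, Section 11.6 and Table 7, and include an assessment at month 3. The existing 4-weekly ticks come close but leave the last scan near day 84, so the month-3 assessment should be named explicitly.

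If 2-monthly imaging is kept, add an analysis of PFS that treats scan-detected progression as interval-censored between the last clear scan and the detecting scan, and report 3-month PFS from it so that the trial's question is unchanged. Moving the landmark to month 4 is not an equivalent repair, because it changes the question asked in Sections 6 and 15.

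It would also help to state in Section 15 how often patients behind the 0.50 reference were assessed.

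The cost is reconciling text and at most the scans already listed in Table 7. The interval-censored option needs only a little more analysis work.

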## 12 Study procedure

### 12.1 Clinical Intervention

Patients on MCT would be monitored for response ( RECIST version 1.1) and toxicity (CTCAE version 4.03) at C1D8, D30 and subsequently monthly till progression.

### 12.2 Laboratory interventions

#### Sample collection:

1. **Tumor tissues will be collected at baseline ( +1 month prior to 2 days post MCT start), C1D8 (+/- 2 days) and at progression.** Fresh(~20-30 mg) and formalin fixed tumor tissues will be used. Tumor content will be assayed and tissues having less than 60% of tumor will not be used for microarray analysis. Fresh tumor tissue will be subjected to extraction of DNA and total RNA while fixed tumor tissues will be used for IHC.
2. **20 ml of blood will be collected (5 ml in 3 EDTA tube and 5 ml in plain tube) at baseline collected at baseline ( +7 days prior to 1 days post MCT start) , C1D8(+/- 2 days) and at progression.** 1 EDTA tube each will be used for Flow cytometry, Microarray and ELISA. Fourth tube will be a reserve. 10 ml of blood will be used for separation of plasma (5 ml) and serum (5ml) which will be stored at -80°C, used for analysis of various parameters.
  - a. PK-PD Sample size collection restricted to stage 1
    - i. 5 ml blood will be collected at each time point. Immediately after collection, blood samples will be kept on ice till they are further process to separate plasma by centrifugation at 4°C. Plasma samples will be stored

at -80°C till further analysis of drug levels (Bioanalysis using LC-MS/MS) and levels of CECs and biomarkers.

| DRUG         | TIME POINTS FOR SAMPLING            | No. of Draws | Cycle and Day |
|--------------|-------------------------------------|--------------|---------------|
| Methotrexate | 0, 0.5, 1, 1.5 , 4, 6, 8, 24, 30 hr | 9            | C1D1,         |

3. **At the time of each monthly D30 (+/- 7 days) follow up 10 ml of blood will be collected in EDTA tube for the first 3 months for Flow cytometry and ELISA .**

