metronomic studies. An modification of this design with bayesian approach and CRM (continuous reassessment model) modelling has been developed and validated by Bhattacharjee et al. (Data sent for publication) It has been validated through data simulation of docetaxel patients where response rate and biomarker was used for decision making. This model takes into account 2 things, disease control (clinical factor) and proportional decline in circulating endothelial cells (biological factor). In the model proposed by Bhattacharjee et al rather than waiting for 3 patients at each dose level, bayesian approach with CRM modelling enables the users to use lesser number of patients and achieve the results early. In this design the efficacy details of each patient are feed into the model and then the model would predict whether the investigators needs to continue at the same dose level or de escalate the doses. The decision rules for the model can be seen in figure 2. This model uses both factors response to MCT and proportional decline in circulating endothelial cells for decision making. Interestingly though response has been used as primary deciding endpoint. In most of the scenarios especially in oral cancers metronomic chemotherapy leads to disease stabilization. In such cases using disease control rate as an criteria for metronomic chemotherapy seems more suitable. Disease control rate is an combination of complete response, partial response and disease stabilization. The variation in CEC measurement is to the tune of 10% or below hence we have used a proportional decline in CEC level of  $> 10\%$  as a deciding factor.

[figure not shown]

Figure 2 : Decision tree.

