### Flow cytometry procedure

#### Timeline for doing flow cytometry

All patients would undergo serum CEC/EPC at least 4 day before administration of oral therapy, then at at D8 (+/- 2 days) , D30 (+/- 5 days), 30 days interval for first 3 months (+/- 7 days) and at progression.

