### Need for multiple biopsies

This genomic analysis will help us to understand the mechanism of action, pathways involved in response and resistance. Three biopsies are required. The reason for these biopsies are

1. The baseline biopsy will help us understand about gene expression in platinum insensitive oral cancers, which genes are upregulated and which are down regulated. This information can not help us in understanding mechanism of action. As the drug exposure has not yet happened. It will gives the baseline state of gene expression in platinum insensitive oral cancers.
2. The biopsy on next visit that is 7th day will then be taken and a gene expression analysis will be done. This gene expression analysis will be compared with the baseline gene expression analysis. This would tell us that after exposure to this combination of MCT\_E which genes are upregulated and which are down regulated. This information will then be used to derive pathways which are upregulated or downregulated post exposure to metronomic chemotherapy. So base on these two biopsies we would get the pathways which are activated or deactivated by MCT ie mechanism of action.

- a. The day 7 biopsy is selected as metronomic molecular actions are genetically expressed by day 6.
3. Now that we would know which pathways are helpful in metronomic action. We would do the third biopsy at progression. The comparison of gene expression of third biopsy would be done with the second one. This will tell us which pathways are responsible for resistance

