## 13 Time and Events Table

All baseline investigations should be performed prior to the start of the chemotherapy. Hematological and biochemical investigations should be obtained within one week of start of chemotherapy. Imaging investigations may be performed within 2 weeks of the start of chemotherapy. All investigations indicated on the chart below will be repeated on the day of the chemotherapy prior to the administration of the chemotherapy.

| Day                                                       | Pre-study | C1D1 | C1D8 | D1 of first 3 cycles | D1 of subsequent cycles | Progression |
|-----------------------------------------------------------|-----------|------|------|----------------------|-------------------------|-------------|
| Eligibility Screen                                        | ✓         | -    | -    | -                    | -                       | -           |
| Informed Consent                                          | ✓         | -    | -    | -                    | -                       | -           |
| Multi speciality Board                                    | ✓         | -    | -    | -                    | -                       | -           |
| History                                                   | ✓         | -    | ✓    | ✓                    | ✓                       | ✓           |
| Physical Examination                                      | ✓         | -    | ✓    | ✓                    | ✓                       | ✓           |
| Toxicity Charting                                         | -         | -    | ✓    | ✓                    | ✓                       | ✓           |
| Complete Hemogram                                         | ✓         | -    | ✓    | ✓                    | ✓                       | ✓           |
| Renal Function                                            | ✓         | -    | ✓    | ✓                    | ✓                       | ✓           |
| Liver Function                                            | ✓         | -    | ✓    | ✓                    | ✓                       | ✓           |
| Serum Electrolytes (Ca 2+ / Mg 2+ ) | ✓         | -    | ✓    | -                    | -                       | -           |
| Biopsy                                                    | ✓         | -    | ✓    | -                    | -                       | ✓           |

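### The protocol gives conflicting baseline sampling windows, one of which allows the CEC tube after treatment has started, although CEC decline is a Stage 1 primary endpoint; the >10% cut-off also ignores two-sample noise.

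*Protocol*

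**What the plan says.** **Baseline blood.** Section 12.2 (Sample collection) sets the blood draw "at baseline collected at baseline ( +7 days prior to 1 days post MCT start", that is, from 7 days before to 1 day after the start. It then assigns the tubes: "1 EDTA tube each will be used for Flow cytometry, Microarray and ELISA". The CEC sample is therefore inside that window.

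Three other places say something different about the same sample:
- Section 12.2 (Timeline for doing flow cytometry): "All patients would undergo serum CEC/EPC at least 4 day before administration of oral therapy".
- Section 3 (Concept sheet, Study procedure): "All patients would undergo serum biomarker investigations at least 1 day before administration of oral therapy". The concept sheet lists CECs among the serum biomarkers.
- Section 13: "All baseline investigations should be performed prior to the start of the chemotherapy". The study calendar puts the ELISA and flow markers at the pre-study visit and not at C1D1.

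**Baseline tissue.** Section 12.2 (Sample collection): "Tumor tissues will be collected at baseline ( +1 month prior to 2 days post MCT start". The section on the need for multiple biopsies describes what the baseline biopsy can show on the footing that "As the drug exposure has not yet happened".

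**Post-treatment sample.** Section 6 puts the CEC decline at D7 of the first cycle, section 15 at D8. The sampling window is D8 +/- 2 days, and Table 3 schedules methotrexate on D1, D8, D15 and D22.

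**Use.** Sections 15 and 16.1 make CEC decline one of twin primary endpoints for the optimal biological dose (OBD), the other being clinical benefit at 2 months.

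**Cut-off.** Section 4.7 takes a decline above 10% as the deciding factor, and the only reason given is "The variation in CEC measurement is to the tune of 10% or below".

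**The concern.** A decline is measured against a baseline, so the baseline has to be free of treatment. A site that follows the sample-collection text can draw the CEC tube the day after the first dose. It would then comply with that text and breach the flow-cytometry timeline, the concept sheet and section 13.

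The protocol itself treats CEC as a pharmacodynamic response. Its C1D1 PK-PD draws at 0 to 30 hours are stored for drug levels and for CECs and biomarkers, so a draw one day after start lies in a period the protocol samples for drug effect. Any early change would enter the baseline only in patients drawn late. Stage 1 has at most 30 patients, 6 at each of 5 levels (section 25), and the dose it selects becomes the Stage 2 dose.

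The second question is whether the 10% cut-off separates a real fall from measurement error. The stated reason compares it with the variation of a measurement, while a decline is the ratio of two measurements.

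**Working it through.** **1. Baseline windows side by side** (days relative to treatment start)

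| Section | Sample | Allowed |
|---|---|---|
| 12.2 Sample collection | blood set incl. flow tube | -7 to +1 |
| 12.2 Flow cytometry timeline | CEC/EPC | -4 or earlier |
| 3 Concept sheet | serum biomarkers | -1 or earlier |
| 13 | all baseline investigations | before start |
| 12.2 Sample collection | biopsy | 1 month before to +2 |
| 12.2 Need for multiple biopsies | biopsy | no drug exposure yet |

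Only days -7 to -4 satisfy all the blood rules. Only the sample-collection text allows a draw after the start.

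**2. Spread of the comparison.** D8 is 7 days after D1. With a baseline from -7 to +1 and D8 +/- 2 days, the interval runs from (7 - 2) - 1 = 4 days to (7 + 2) + 7 = 16 days.

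**3. Direction of a late-baseline bias.** Let d be the true fall by D8 and f the share of it already present at a late draw. The measured fall is 1 - (1 - d)/(1 - f*d). This is less than d whenever f > 0. The documents give neither d nor f, so the size cannot be derived.

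**4. D8 sample.** Section 13 has charted investigations done before administration on a chemotherapy day, and the calendar lists both the flow markers and treatment at C1D8. A draw on D8 itself is therefore already pre-dose. What remains is D9-D10, which falls after the second methotrexate dose if that dose is taken on schedule.

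**5. The cut-off against two-sample noise.** The protocol gives no error rate for the CEC rule, so there is no figure to reproduce. Assumptions: the quoted variation is a per-sample CV, errors are independent and log-normal, there is one sample per time point, and no day-to-day biological variation is added.
- sigma = sqrt(ln(1 + CV^2)).
- SD of the log ratio D8/baseline = sqrt(2) x sigma.
- P(decline > 10% given no true change) = Phi(ln 0.90 / (sqrt(2) x sigma)).
- At CV 10%: sigma = 0.0998, SD = 0.141, ln 0.90 = -0.105, z = -0.747, P = 22.8%. A simulation of 2,000,000 pairs with normal errors gives 22.9%.
- Cut for a one-sided 5% rate = 1 - exp(-1.645 x SD). At CV 10% this is 1 - exp(-0.232) = 20.7%.

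| Per-sample CV | False decline, one patient | Cut for one-sided 5% |
|---|---|---|
| 10% | 22.8% | 20.7% |
| 7% | 14.3% | 15.0% |
| 5% | 6.8% | 11.0% |
| 3% | 0.7% | 6.7% |

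The 10% cut holds the false-decline rate to 5% or less only if the CV is about 4.5% or lower.

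Other readings of the 10%:
- As a 95% limit for one measurement, CV = 10/1.96 = 5.1% and the rate is 7.2%.
- As a 95% limit for a difference, CV = 10/(1.96 x sqrt(2)) = 3.6% and the rate is 1.9%.

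If the rule uses the mean log ratio of n patients, z is multiplied by sqrt(n). At CV 10% the rate is 9.8% for n = 3 and 3.4% for n = 6 (z = -0.747 x 2.449 = -1.83).

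**The case against.** **On timing.** Section 13 already states the right principle, the calendar agrees with it, and the flow-cytometry timeline is the assay-specific text; the sample-collection window is the lone outlier. That stands, and it makes the repair easy. It does not remove the conflict, because the outlier is the text that tells staff when to draw the tubes.

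A day-1 effect may also be small: the biopsy rationale speaks of molecular actions being expressed by day 6. No size can be claimed either way. If half the fall had already occurred, a true 15% fall would read 1 - 0.85/0.925 = 8.1% and a true 20% fall 1 - 0.80/0.90 = 11.1%. These lie on opposite sides of the cut-off, and the half is pure assumption.

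**On the cut-off.** A reader might infer that the 10% cut-off lies inside assay noise and that Stage 1 CEC decline is therefore unreliable. The documents do not support this:
- Section 4.7 says 10% or below and does not define the variation. At a CV of 3%, or if 10% is already a limit for a difference, the cut-off is adequate.
- Section 15 speaks of continuously updated posterior estimates of CEC decline, which may pool patients, and the decision tree (Figure 2) is not shown. Labelling patients one by one cannot be assumed.
- Assay noise applies alike at every dose level, and CEC is only one of two endpoints. Nothing shows that these errors would decide the OBD.

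What remains of the cut-off point is that the stated reasoning leaves out the second sample, and that day-to-day biological variation, for which no figure is given, could only add noise.

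**Conclusion.** The timing conflict is established from the text. The baseline CEC tube may be drawn up to 1 day after the start under one section and must precede treatment under three others. The biopsy window, to 2 days after the start, contradicts the premise of no drug exposure. Because CEC decline is a twin primary endpoint for the OBD, a late baseline can bias it in the patients concerned. It pulls the decline towards zero if CEC has already begun to fall, by an amount the documents do not let one calculate. D7 in section 6 and D8 in section 15 also disagree.

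The cut-off point is secondary and conditional. The cut-off may lie inside two-sample noise: the single-patient false-decline rate runs from 22.8% (CV 10%) to 0.7% (CV 3%), and pooling six patients at CV 10% brings it to 3.4%. These figures rest on reading the variation as a per-sample CV with independent errors.

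**What to change.** - **Baseline.** Reconcile section 3, both parts of section 12.2 and section 13 to one window, with an earliest and a latest day, in which every baseline blood and tissue sample precedes the first dose.
- **Post-treatment sample.** Use one day label in sections 6 and 15. Keep the pre-dose rule for D8 and close the D9-D10 tail, for example by requiring the sample before the second methotrexate dose whenever it is taken.
- **Cut-off.** State what the 10% measures: CV or limit, one sample or a difference, analytical only or including day-to-day variation. Then either enter the log ratio D8/baseline in the Stage 1 model as a continuous quantity, or derive the cut from the SD of a two-sample difference, sqrt(2) x CV.

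The cost is protocol and laboratory-manual wording, slightly tighter sampling logistics and at most a small model change. It should be done before the first dose-level decision, since a baseline taken after the first dose cannot be recovered.
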